### Data collection

4.4

#### Psychobehavioural variables – psychometric measures

4.4.1

In addition to anamnestic data, the following previously validated instruments showing good psychometric properties will be applied:

Self-efficacy: The Self-Efficacy Scale (SWE (100)) is a self-report instrument for measuring general optimistic self-confidence. It consists of 10 items and measures optimistic competence expectancy, i.e., confidence in solving difficult situations with one’s own abilities.

General substance related craving: The MaCS (Mannheim Craving Scale (101)) is an instrument for measuring substance related craving. It consists of 12 items and four additional items and is rated on a 5-point Likert scale.

Tobacco dependence: The Fagerström Test for Cigarette Dependence (formerly Fagerström Test for Nicotine Dependence; FTND (102)) is a self-assessment instrument measuring tobacco dependence intensity. It consists of 6 categorically scaled items that assess the number of smoked cigarettes per day (CPD), compulsive use, and dependence intensity.

Psychiatric Symptoms: For the evaluation of psychopathology, the ICD-10 Symptom Rating (ISR (103)) questionnaire was utilized. In accordance with the ICD-10, this self-assessment questionnaire, comprising 30 items, is designed to comprehensively assess the status and severity of mental disturbances. Symptoms of the six symptomatic patterns – depressive, anxiety, obsessive-compulsive, eating disorders, somatoform syndrome, and post-traumatic stress disorder – are assessed.

Primary Affects: The German version of the Brief Affective Neuroscience Personality Scales including a LUST Scale (BANPS–GL (104)) is a self-report questionnaire to measure all seven primary affects proposed by Jaak Panksepp (105) as personality traits.

Smoking behaviour: As previously in the pilot study, participants will be asked regarding their daily smoked cigarettes in the last two weeks (interval scaled). A second, dichotomous single-item question will assess if participants have been completely abstinent from tobacco smoking in the last two weeks.

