#### Gut microbial domain

2.1.3

In line with previous studies, we hypothesize that smoking contributes to gut microbial imbalances, reduced general bacterial diversity and abundance of commensals, and growth of pathogens (91). We hypothesize that reversed effects in these imbalances will be observable after smoking cessation. Further emphasis will be put on the identification of microbial markers corresponding with general substance craving, history of smoking and success of smoking cessation. Gut microbial correlates of primary emotions and psychiatric symptoms will be identified in exploratory analyses. Analyses will further focus on bacterial genera with a known role (as derived from literature) in the metabolism of SCFA, PUFA, bile acids, and tryptophan (metabolites) (20). Combined metabolome-microbiome analyses will ascertain associations between bacterial abundances and concentrations of relevant metabolites.

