### Type and design of the study

4.1

The present study is a randomized controlled experiment in N = 100 SUD- inpatients during a therapeutic community treatment with one intervention group that will receive an additional 6-week smoking cessation intervention and one control group that will receive treatment as usual. The study design consists of a 2 x 2 mixed subject design with repeated measures for the biological analyses and a 2 x 3 mixed subject design with repeated measures for the psychobehavioural analyses (see **Table 1**). In both groups, an examination of metabolic and gut microbial profiles, as well as psychological variables, will take place. Biological parameters will be ascertained from blood and stool specimens for nuclear magnetic resonance (NMR) spectroscopy metabolomic analyses and from stool specimens for 16s-mRNA (hypervariable V3-V4 regions) sequencing and subsequent gut microbial profiling. Psychobehavioural and biological data will be collected pre & post smoking cessation, and additionally, there will be a follow-up measurement of the psychobehavioural variables 3 months upon completion of the study (see **Figure 3**: Consort Flow Chart for further illustration).

**Table 1 T1:** Overview of the statistical design.

Study group	Pre- intervention baseline	Post- intervention after 6 weeks	Follow- up after 3 months
Intervention Group (N = 50)	Psychobehavioural Data	Psychobehavioural Data	Psychobehavioural Data
	Metabolic/Microbial Data	Metabolic/Microbial Data	
Control Group (N = 50)	Psychobehavioural Data	Psychobehavioural Data	Psychobehavioural Data
	Metabolic/Microbial Data	Metabolic/Microbial Data	

green cells: biological data; light brown cells: self-report data.

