### Intervention

4.3

During the inpatient stay at the ‘Grüner Kreis’ community, the patients will be allocated to an intervention group and a control group. Patients of the intervention group will take part in an additional 6-week behavioural therapy program for smoking cessation. Patients of the control group will undergo treatment as usual. The standard treatment within this therapeutic community—which all participants will receive—consists of group therapy (once a week), individual psychotherapy (once a week), counseling by social workers, psychiatric consultations, as well as sport-, art- and work therapy. For further information on the principles of therapeutic community-based addiction treatment, see, e.g., DeLeon & Unterrainer (36).

The “smoke free in 6 weeks” program is a standardized behavioural therapy intervention (see Batra & Buchkremer (99) for detailed instructions) that takes place once a week for 1.5 hours over 6 weeks and is provided by the Austrian health insurance provider *Österreichische Gesundheitskasse* (ÖGK). Held in the therapeutic community, it will employ principles of cognitive-behavioural therapy (CBT) coupled with personalized recommendations for nicotine replacement. The Austrian health insurance standard for therapy will be guiding the program’s content, which is tailored for inpatient clients. Specifically, the following interventions based on CBT techniques will be applied in the weekly group sessions consisting of 10 to 15 participants: Psychoeducation including information on tobacco addiction, health risks, advice on relapse prevention and the handling of craving, motivation building, behavioural observation, setting a personal quit-smoking day, behaviour modification through the development of alternative actions, training of progressive muscle relaxation, strengthening of self-efficacy and information on the topics of physical activity and nutrition. Finally, to increase intrinsic motivation, each session will include an analysis using a calibrated carbon monoxide measurement. The primary aim is to help clients achieve smoking cessation, favouring this approach over gradual reduction methods. To support ongoing abstinence and motivation, participants will be directed to additional resources such as the Smoke-Free App, Smoke-Free Phone, and regional outpatient cessation services. This program will be led by a clinical psychologist who is specifically trained in conducting the program.

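### Abstinence and cigarettes per day are unverified self-report in a trial that cannot be masked, and exhaled CO is described only in the intervention sessions, so misreporting can differ by arm, in either direction

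*Protocol article*

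**What the plan says.** Section 4.4.1 (psychometric measures) defines smoking behaviour by two questions covering the past two weeks. The first asks for the number of cigarettes smoked daily. The second concerns abstinence: "A second, dichotomous single-item question will assess if participants have been completely abstinent from tobacco smoking in the last two weeks". The third tobacco measure, the Fagerström test, "is a self-assessment instrument measuring tobacco dependence intensity". The legend of Table 1 (section 4.1) gives only two kinds of data: "green cells: biological data; light brown cells: self-report data". The psychobehavioural data, which include smoking, belong to the second kind.

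CO appears in one place, the description of the course in section 4.3: "to increase intrinsic motivation, each session will include an analysis using a calibrated carbon monoxide measurement". Only the intervention group attends these weekly sessions. The components listed for treatment as usual include no CO reading. The course is also "coupled with personalized recommendations for nicotine replacement".

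The smoking data are used in four places:
- Section 2.1.1, as part of the secondary aim, judges the long-term success of the intervention by group differences at 3 months.
- Section 4.7.4 models cigarettes per day as an ordinal outcome by GEE.
- Section 4.7.5 names cigarettes per day as a variable to be related to bacterial taxa in MaAsLin2.
- Section 2.1.3 seeks microbial markers that correspond with, among other things, "history of smoking and success of smoking cessation".

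Section 4.7.7 lists the measures against bias: randomisation, a control group, a shared facility, and attention to diet and medication. It mentions neither masking nor verification of smoking status.

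**The concern.** A weekly group course set against treatment as usual cannot be hidden from participants. One arm sets a quit day, is coached towards complete cessation and sees its own CO reading every week. The other arm has none of this. Both arms then answer the same unverified questions. The conditions under which the answers are given differ by arm, so the error in the answers can differ too. Randomisation does not protect against that.

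Two things are at stake. The between-arm results on abstinence and cigarettes per day could be partly or wholly a difference in reporting. In addition, any analysis that sorts participants by reported smoking status, or uses reported cigarettes per day as a predictor, would work with misclassified exposure. The 3-month comparison is the most exposed, because by then the course and its readings have ended and no biological sample is taken.

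**Working it through.** **Plan's own figure.** There is none to reproduce. The article states no expected abstinence rate, no misreporting rate and no power for a smoking outcome. The sample size calculation in section 4.7.1 concerns a mixed-design ANOVA and plays no part here.

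**Step 1: is any check of smoking status described?** Setting the sections side by side:
- 4.4.1 and Table 1: smoking data are self-reported at baseline, 6 weeks and 3 months.
- 4.3: CO is measured at sessions, in one arm, for motivation.
- 4.4.3 and 4.7.6: blood and stool are collected before and after the intervention for metabolome and microbiome profiling. The list of target metabolites in 4.7.6.1 names no nicotine marker, and no sample is assigned to check smoking status.
- 4.1 and 4.2: at 3 months only psychobehavioural variables are collected.

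No section describes a check, and the one relevant device is described in one arm only.

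**Step 2: size, by assumption.** Let p be true abstinence, equal in both arms, and let q be the share of continuing smokers who falsely report abstinence. Then:

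reported abstinence = p + (1 − p) × q

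spurious difference = (1 − p) × (q in arm A − q in arm B)

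With p = 0.10:
- q = 0.10: 0.10 + 0.90 × 0.10 = 0.190
- q = 0.02: 0.10 + 0.90 × 0.02 = 0.118
- q = 0.05: 0.10 + 0.90 × 0.05 = 0.145
- q = 0.20: 0.10 + 0.90 × 0.20 = 0.280

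| q, arm A vs arm B | Reported abstinence | Spurious difference |
|---|---|---|
| 10% vs 10% | 19.0% vs 19.0% | 0 points |
| 10% vs 5% | 19.0% vs 14.5% | 4.5 points |
| 10% vs 2% | 19.0% vs 11.8% | 7.2 points |
| 20% vs 5% | 28.0% vs 14.5% | 13.5 points |

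Arms A and B are interchangeable. If the control arm over-reports more, the same differences favour control.

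**Step 3: effect on a test.** Section 4.7.4 plans chi-square tests for categorical variables, and Table 1 gives 50 per arm. The table shows the exact probability that a two-sided 5% chi-square test rejects although true abstinence is equal:

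| q, arm A vs arm B | p = 10% | p = 20% |
|---|---|---|
| 10% vs 10% | 0.05 | 0.05 |
| 10% vs 0% | 0.26 (9 points) | 0.16 (8 points) |
| 20% vs 5% | 0.39 (13.5 points) | 0.26 (12 points) |
| 20% vs 0% | 0.66 (18 points) | 0.43 (16 points) |

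The rows with 0% are deliberately stark contrasts. They show how the error grows and are not a forecast for this trial.

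**Step 4: blurring of analyses by smoking status.** Among those who report abstinence, the share still smoking is (1 − p) × q divided by reported abstinence. With p = 0.10 this is 0.018 / 0.118 = 15% for q = 2%, 0.045 / 0.145 = 31% for q = 5%, and 0.090 / 0.190 = 47% for q = 10%. This loss arises even when misreporting is equal in the two arms.

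**The case against.** **Direction.** A reader might infer that coaching makes the intervention arm over-report, so that the bias runs towards benefit. The article does not support that. Weekly CO readings may make that arm's answers more accurate. Controls also had to state that they want to quit (section 4.5) and live in the same community, so they too have a reason to over-report. Only the statement that misreporting can differ by arm stands.

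**Reach.** A reader might also infer that the abstinence item defines cessation success for the microbial work. Section 2.1.3 gives no definition, and the abstinence item does not appear in Table 2. The smoking variable that section 4.7.5 names for the taxon models is cigarettes per day. The main biological comparisons are by randomised arm: ANCOM-BC in 4.7.3, the Kruskal-Wallis tests in 4.7.5 and the group effects in 4.7.2. Misreported smoking does not touch these. The central hypotheses in the abstract concern self-efficacy and craving, and the long-term success of cessation belongs to the secondary aim. All of this stands and narrows the point to the smoking results and the exploratory associations.

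**Feasibility.** The course is run by the health insurer, so the meter may be available only during sessions. Section 4.6 speaks of online questionnaires, and an in-person visit at 3 months is not documented. This stands against any claim that the change is free. It does not apply to an in-person contact at baseline and 6 weeks, because both arms travel to the research centre for samples then (section 4.2).

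**Fit.** CO may not cover the two-week recall period and cannot validate a count of cigarettes. A baseline reading does not address reporting that differs by arm, since baseline questionnaires precede randomisation. This also stands, so CO supplements self-report and does not replace it.

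**Article length.** It could be said that verification was left to a fuller protocol. The article, however, spells out its smoking measures and gives the CO device a different stated purpose, so this is a described design choice.

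**Conclusion.** The point holds in limited form. As written, abstinence and cigarettes per day are unverified self-report in a trial that participants cannot be masked to, and CO is described in one arm only, for motivation. Masking is an inference from the design, since the article does not discuss it. Misreporting can therefore differ by arm and can bias the between-arm smoking results in sections 2.1.1 and 4.7.4. It can also blur the exploratory analyses that use smoking status or cigarettes per day (sections 2.1.3 and 4.7.5). Biological comparisons by randomised arm are not affected.

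This is a risk and not a demonstrated bias. With 10% true abstinence in both arms and false reports by 10% against 2–5% of continuing smokers, the spurious difference is about 4.5–7 points in favour of whichever arm over-reports. With equal misreporting it is nil. All these rates are assumptions. The improvement is worthwhile because it is small and uses a type of device already in the trial.

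**What to change.** Take one exhaled-CO reading in both arms, under the same procedure, at the in-person baseline and 6-week assessments, and at 3 months wherever participants are seen in person. Define CO-supported abstinence as self-reported abstinence plus CO below a cut-off stated before data collection. Report it alongside self-report, and use it in the analyses by smoking status. Record use of nicotine replacement at the same visits: the course includes recommendations for it, CO does not reflect it, and the hypotheses concern nicotine. Label outcomes without a reading, and cigarettes per day throughout, as unverified self-report.

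Cost: 100 participants × 2 visits = 200 brief breath readings, plus up to 100 at 3 months, and a short amendment. Access to a meter outside the insurer-run course must be confirmed. Some 3-month readings will be missing. CO does not cover the full two-week window and does not validate cigarette counts. Reported quit rates may come out somewhat lower. If readings prove infeasible, labelling the smoking outcomes as unverified is the minimum.

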#### Dietary assessments

4.4.2

Dietary assessments will be performed using the Vienna Food Record (106) a food frequency questionnaire which takes Austrian-specific eating habits into account. Participants will be asked to document their food intake during the week prior to the assessments of blood and stool.

#### Collection of biological samples

4.4.3

In order to collect the blood and stool samples, participants will be instructed to fast for at least 12 hours prior to venipuncture, and the blood samples will be drawn in the morning.

A maximum of 70 ml, equivalent to approximately 5 tablespoons of blood, will be collected into EDTA-coated tubes. Blood samples will be centrifuged at 4 °C for 15 minutes at 4000 rpm within 30 minutes of phlebotomy, and plasma aliquots will be immediately frozen at −80 °C until analysis.

Furthermore, approximately 1 g of stool will be collected from each participant in with stool sample kits with DNA/RNA stabilization buffer ensuring stabilization of microbial DNA at ambient temperature (OMNIgene^®^GUT, DNA Genotek Inc., Canada), immediately frozen and stored at -80 °C until further processing. For information regarding the further processing and downstream analyses of the biological data, see 4.7.5 and 4.7.6.

### Inclusion and exclusion criteria

4.5

*Inclusion Criteria:* Participants must provide informed consent. They must have a diagnosis of a form of substance use disorder (F1x.x) by a licensed psychiatrist according to ICD-10 (98). Participants must be at least 18 years old, can be of either sex, and must have sufficient knowledge of the German language. All participants must explicitly express their willingness to quit smoking. A minimum duration of abstinence from the primary substance and stable dosage of long-term medications for at least 3 months prior to inclusion is mandatory.

*Exclusion Criteria* include lack of consent, age below 18, or inability to provide informed consent. Participants with acute psychotic symptoms or acute suicidal tendencies are also excluded. Further exclusions are cardiovascular disease, pregnancy or breastfeeding, severe mental or organic illnesses (such as epilepsy, brain tumours, recent major surgery), tumour diseases, dementia (Mini Mental Score <20), severe autoimmune diseases or immunosuppression, acute infections, or acute diarrhea. Individuals with prior gastrointestinal surgery (except appendectomy), probiotic intake within the last 6 months, or those consuming dietary supplements, probiotics, antibiotics, or prebiotic supplements during the study will also be excluded.

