#### Controlling for potentially confounding variables, and multiple testing

4.7.3

Proper analysis of the research questions in the SUD sample will be hampered by several sources of variance, such as diet, psychiatric diagnoses, medications, and history of substance misuse. These variables will be held constant as control variables.

Psychiatric comorbidity is highly present in the population. Psychiatric symptom burden and classes of psychiatric diagnoses are associated with systematic metabolic and microbiome profiles (72, 113, 114). Classes of psychiatric secondary diagnoses (mood, anxiety, psychotic, and neurodevelopmental disorders) will therefore be considered as covariates. Intake of psychotropic medications are respectively frequent. The literature shows reciprocal interactions between psychotropic medications and gut microbiota (115), and metabolic patterns in response to treatment (116, 117). Type of medication class intake (antipsychotics, antidepressants, antianxiety drugs, anticonvulsants/mood stabilisers, opioid substitution) will be considered as covariates. Length and consumption patterns from SUD history will also enter covariate analysis (with regard to substances – primarily consumed substances vs. polytoxicomania). These covariates will be entered in Multi-omics factor analysis (MOFA) in direct joint modeling (118) to ensure that observed microbiome–metabolome–psychological associations are not driven by covariate effects. For the microbiome domain, intervention vs. control group comparisons regarding microbial abundance and composition will be performed with Analysis of Compositions of Microbiomes with Bias Correction (ANCOM-BC), a package which allows for continuous and categorical covariate adjustment within a linear regression framework, and was designed to analyze longitudinal data (119).

Metabolome and microbiome studies involve the examination and statistical testing of a multitude of variables. Thus, controlling for multiple testing is a must; False Discovery Rate corrections will be based on statistical recommendations promoting flexible algorithms within the R package FDRestimation (120).

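### Section 4.5 sets a 6-month look-back for probiotics but bars antibiotics only during the study, so a course finished just before the baseline stool sample is allowed, with no stated record or adjustment

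*Protocol article*

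**What the plan says.** Section 4.5 (Inclusion and exclusion criteria) handles these products in one sentence with two different time frames. It excludes those with "probiotic intake within the last 6 months, or those consuming dietary supplements, probiotics, antibiotics, or prebiotic supplements during the study will also be excluded". The first clause, on probiotics, looks back before entry. The second looks only forward. Antibiotics appear only in the second clause, and nowhere else in the article.

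Three other provisions come close:

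- Section 4.5 also excludes "acute infections, or acute diarrhea".
- Section 4.5 requires that "stable dosage of long-term medications for at least 3 months prior to inclusion is mandatory".
- Section 4.7.3 lists the medication covariates: "Type of medication class intake (antipsychotics, antidepressants, antianxiety drugs, anticonvulsants/mood stabilisers, opioid substitution) will be considered as covariates".

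Section 4.1 and Table 1 schedule microbiome sampling twice, before the intervention and after 6 weeks. Each participant's change therefore rests on a single baseline sample.

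**The concern.** The plan itself treats antibiotics as disruptive enough to exclude anyone who takes them during the study, and it treats exposure before entry as relevant over 6 months for probiotics. Leaving antibiotics without any window before baseline does not fit with either position.

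The baseline sample is what is at stake. Section 2.1.3 hypothesises that cessation reverses reduced bacterial diversity and loss of commensals. If a participant's microbiome is recovering from antibiotics during the 6 weeks, that recovery could resemble the hypothesised change. It would add noise to the comparison between groups. It would also be mixed into any within-group comparison over time, such as the longitudinal LEfSe analysis planned in section 4.7.5.

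**Working it through.** **Does any other provision close the gap?**

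- The exclusion of acute infection and acute diarrhoea (4.5) concerns illness present at entry. A resolved infection with a completed course passes.
- The 3-month stability rule (4.5) applies to long-term medication. A short course is not long-term medication.
- The medication classes in 4.7.3 are psychotropic drugs and opioid substitution. The other named covariates are diagnosis classes, substance-use history and diet, with sex added in section 8. None captures prior antibiotics.
- The dietary record (4.4.2) covers food over one week.
- Section 4.7.7 promises explicit attention to confounders such as medication, but refers back to 4.7.2 and 4.7.3, which do not name antibiotics.
- Section 4.4.1 mentions history-taking ("In addition to anamnestic data, the following previously validated instruments") without listing its content. Prior antibiotics are neither named nor ruled out.

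So eligibility is open on this point, and no record or adjustment is stated.

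**How large could the effect be?** The plan has no figure to reproduce. What follows is an illustration.

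Assumed inputs, not in the documents: share p with a recent course, 5% to 20%; shift D in their pre-post change, 0.5 to 2 SD of change, the same in both arms. From the plan: 50 per group (Table 1), about 45 after 10% attrition, and a stated minimum of 46 per group (4.7.1).

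Variance of change, relative to 1 without the exposure: V = 1 + p(1 − p)D². Loss of effective sample size for a comparison of mean changes: 1 − 1/V.

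| p | D | V | Loss of effective n |
|---|---|---|---|
| 0.05 | 0.5 | 1 + 0.0475 × 0.25 = 1.012 | 1.2% |
| 0.05 | 1 | 1 + 0.0475 × 1 = 1.048 | 4.5% |
| 0.10 | 1 | 1 + 0.09 × 1 = 1.09 | 8.3% |
| 0.10 | 1.5 | 1 + 0.09 × 2.25 = 1.203 | 16.8% |
| 0.20 | 2 | 1 + 0.16 × 4 = 1.64 | 39.0% |

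Chance imbalance: the resulting difference between arms has SD = D√(2p(1 − p)/n). With n = 46 this is 0.5 × √(2 × 0.0475/46) = 0.023 at the low end and 2 × √(2 × 0.16/46) = 0.167 at the high end, in SD units of change. This is the same added variance seen from another side, so the two must not be added together.

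Power: for an assumed true difference of 0.5 SD of change, a two-sample comparison of mean changes with 46 per group has power 0.67 without the exposure. With it, power is 0.66 at the low end (SD × 1.006) and 0.47 at the high end (SD × 1.281).

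**Does this carry over to the planned tests?** Only roughly. Section 4.7.5 compares alpha diversity by Kruskal-Wallis, which is rank-based, and beta diversity by db-RDA on distance matrices. The formula above is for a mean change.

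**The case against.** Several objections carry weight.

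- **A reader might infer that prior antibiotic use goes unrecorded and cannot be adjusted for.** The article does not support that. It collects history data of unspecified content, and a journal article commonly leaves such items to the full protocol or case report form. What can be said is that no record or adjustment is stated.
- **A reader might infer that the group comparison is biased in favour of the hypothesis.** It is not. Section 4.2 allocates by block randomisation, so prior use is equal between arms in expectation. Randomisation does not protect within-group change over time.
- **The size rests on assumptions.** Prevalence, shift and recovery time are not in the documents. That recovery shows within 6 weeks, and in the hypothesised direction, is itself an assumption. The upper end needs one participant in five exposed and a 2 SD shift.
- **Other exclusions narrow the exposed group.** Acute infection, recent major surgery, immunosuppression and prior gastrointestinal surgery probably remove some recent users, though not someone who has simply completed a course.
- **A covariate has limits.** At 5% prevalence it would be positive for 2 or 3 people per arm, and Kruskal-Wallis takes no covariate.
- **The aims are described as largely exploratory (section 2),** which lowers the importance.

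These points limit the size and the wording. They do not remove the mismatch, because it lies in an eligibility rule that the article states in full.

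**Conclusion.** The point holds as a minor one. Followed exactly, section 4.5 admits a participant whose antibiotic course ended just before baseline, while excluding one who took a probiotic five months earlier. Nothing else in the article covers that exposure.

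The consequences are added variance, possible chance imbalance with about 45 to 50 per arm, and within-group longitudinal results that cannot be separated from recovery after antibiotics. Under the assumed ranges (5% to 20% exposed, shift 0.5 to 2 SD), the variance of change rises by about 1% to 64%. The documents do not show where in that range this trial lies.

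**What to change.** Ask about antibiotic courses before baseline with one screening question. The look-back already used for probiotics is one possible window, but its length is for the investigators to set. Then:

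- include recent use (yes/no) as a covariate in the db-RDA, MaAsLin2 and ANCOM-BC models;
- for alpha diversity, either repeat the Kruskal-Wallis comparison without recent users as a sensitivity analysis, or replace it with a regression that takes the covariate;
- repeat the longitudinal LEfSe comparison without recent users.

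Alternatively, state a pre-baseline antibiotic window in section 4.5, consistent with the probiotic clause. If the full protocol or case report form already records prior antibiotics, saying so and naming the adjustment is enough.

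The cost is one screening item and one covariate, which will be estimated poorly if few participants are exposed. Regression for alpha diversity would also mean changing the planned test. If the window is used as an exclusion, a few otherwise eligible patients are lost. The question is best asked at baseline, since later recall is less reliable.
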